##### 3.2.2 Secondary Outcomes

- Changes in participant rated symptoms of eczema

Patients are asked to record the severity scores of itchiness and sleep disturbance of the previous day in a diary card (10 point scale from 0-none to 10-extreme) (supplement 4)

- Changes in the need of eczema treatment

Patients are asked to record the use of topical steroids, antihistamines, oral steroids or immunosuppressive drugs on a diary card. (supplement 4)

- Immunological serum markers:

Changes in serum total IgE, specific IgE to enterotoxin A,B, C and TSST (staphylococcus enterotoxins) serum eosinophil cationic protein (ECP), blood eosinophils, C reactive protein. Changes in cytokine serum levels (RANTES, IL-31, IL-18,IL-16).

- Changes in skin microflora

Characterize the skin microflora of determined areas and determine the changes in number of colony forming units of *Staphylococcus aureus* from the beginning to the end of study.

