## 7. Study Schedule

Visit 0:

- Explain study protocol
- Review medical history to determine eligibility based on inclusion/exclusion criteria.
- Schedule visit 1

Visit 1 :

- Provide written information about the study
- Obtain signature of potential subject on written informed consent
- Perform medical examination and register SCORAD index
- Answer a quality of life questionnaire
- Patients are explained and given a diary symptoms card
- Perform skin swab of determined areas
- Perform serum sampling
- Patients are explained trial and are given a TShirt and pants
- Surveillance and medical care, if required

Visit 2 :

- Review medical history including medications history
- Perform medical examination and register SCORAD index
- Answer a quality of life questionnaire
- Deliver the diary symptoms card
- Perform skin swab of determined areas
- Perform serum sampling

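### Two diary-based secondary outcomes are defined as changes, but no pre-treatment diary period is scheduled and no reference value is defined

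*Protocol*

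**What the plan says.** Protocol section 3.2.2 names two secondary outcomes as changes, "Changes in participant rated symptoms of eczema" and "Changes in the need of eczema treatment". The data source for both is a diary card. For the first: "Patients are asked to record the severity scores of itchiness and sleep disturbance of the previous day in a diary card", on a scale from 0 to 10. For the second: "Patients are asked to record the use of topical steroids, antihistamines, oral steroids or immunosuppressive drugs on a diary card". The second has no stated recall window.

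Section 7 places the card within three visits:

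- **Visit 0** explains the study, schedules Visit 1 and includes "Review medical history to determine eligibility based on inclusion/exclusion criteria". It has no diary.
- **Visit 1** includes both "Patients are explained and given a diary symptoms card" and "Patients are explained trial and are given a TShirt and pants".
- **Visit 2** includes "Deliver the diary symptoms card" and is the only visit at which a medication history is named.

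Section 4 describes one screening visit and one visit at each end of an eight-week period, with the garments worn at night. It mentions no run-in. Section 3.2.1 describes SCORAD, whose part C scores itch and sleeplessness from 0 to 10 each. Section 7 registers SCORAD at Visits 1 and 2.

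**The concern.** A change needs a starting value. SCORAD, quality of life, serum markers and skin swabs are all scheduled at both Visit 1 and Visit 2, so each has a start and an end. The diary does not: it begins when treatment begins. An analysis plan can choose a model and a summary measure, but it cannot supply pre-treatment observations that the visit schedule never asked for.

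Two things follow:

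- If the first days or week of the diary serve as the baseline, whatever the textile has already done by then is subtracted from its measured effect.
- If the reference entries are left open, they could be picked after the data are seen.

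Treatment need is also the outcome that helps interpret SCORAD, because it shows whether the arms differed in their use of topical steroids or other drugs. It should be defined in a way the collected data can support.

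**Working it through.** **Step 1. Outcome definitions against the schedule (sections 3.2.1, 3.2.2, 4 and 7).**

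| | Itch and sleep | Treatment use |
| --- | --- | --- |
| Diary days scheduled before Visit 1 | 0 | 0 |
| Pre-garment days reachable by recall | at most 1 (previous-day recall) | none stated |
| Other scheduled Visit 1 measure | SCORAD part C, a different instrument | none named |
| Entry or period named as the reference | none | none |

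The single recalled day arises because symptom entries refer to the day before and the garment is worn at night. An entry made at or just after Visit 1 could describe a day before the first night in the garment. The protocol does not say when the first entry is made.

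**Step 2. An effect size for illustration.** Section 8.2 gives a significance level of 0.05, power of 0.8 and 90 patients, but no mean difference, SD, sidedness or allocation ratio. The 90 therefore cannot be reproduced. It can only be solved backwards, assuming 1:1 allocation (45 per arm) and a normal approximation:

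d = (z for alpha + z for power) × √(2/45)

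- Two-sided: (1.960 + 0.842) × 0.2108 = 0.591 SD
- One-sided: (1.645 + 0.842) × 0.2108 = 0.524 SD

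The two-sided value is used below. It was implied for SCORAD, so applying it to a diary outcome is a further assumption.

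**Step 3. Loss from an on-treatment baseline.** Let f be the fraction of the effect already present in the diary days used as baseline. The change score then carries d(1 − f). With the change-score SD equal to the outcome SD, power = Φ(d(1 − f)√22.5 − 1.96), where √22.5 = 4.743.

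| f | d(1 − f) | Noncentrality | Power |
| --- | --- | --- | --- |
| 0 | 0.591 | 2.80 | 80% |
| 10% | 0.532 | 2.52 | 71% |
| 25% | 0.443 | 2.10 | 56% |
| 50% | 0.295 | 1.40 | 29% |

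**Step 4. How much the SD assumption matters.** The variance of a change score relative to the outcome is 2(1 − r), where r is the correlation between baseline and later diary values. Step 3 corresponds to r = 0.5. Dividing the effect by √(2(1 − r)) gives:

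| f | r = 0.3 | r = 0.5 | r = 0.7 |
| --- | --- | --- | --- |
| 0 | 66% | 80% | 95% |
| 10% | 57% | 71% | 90% |
| 25% | 43% | 56% | 77% |
| 50% | 22% | 29% | 44% |

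An unadjusted comparison of on-treatment levels has 80% power on the same assumptions. The contaminated change score does worse in eight of the nine cells with f above 0. The exception is f = 10% with r = 0.7. The reduction of the measured effect by the fraction f does not depend on r.

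**The case against.** The strongest reply is that little is lost. Randomisation makes a between-arm comparison of on-treatment itch, sleep scores or drug use valid with no baseline, and the planned diary collects those data. The word for change appears in the outcome titles, while the text under them says only what is recorded. How a diary is summarised is commonly left to an analysis plan, and nothing in the protocol prescribes early on-treatment days as the reference. All of this stands. It confines the problem to the definition and leaves the trial's ability to compare the arms intact.

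A reader might infer two stronger things that the documents do not support.

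- **That no pre-treatment information on symptoms exists at all.** Previous-day recall may give one pre-garment day, and SCORAD part C records itch and sleeplessness at Visit 1. Neither is named as the baseline, one day is thin for a fluctuating disease, and part C is a separate instrument, but both exist.
- **That the trial could not tell whether a SCORAD difference came with greater steroid use.** On-treatment use compared between arms answers that directly.

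On medication, Visit 0 reviews medical history, Visit 2 does not limit the period its medication history covers, and section 11.2 enters concomitant medications in the data system. The diary layout (supplement 4) is not shown, and section 6.4 breaks off in the text available. Some pre-treatment information may therefore be captured in practice. What can be said is that no pre-treatment record of eczema treatment is scheduled or named as a baseline.

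The power figures are also open to challenge. The protocol gives neither the effect size nor the carry-over, and the trial was not sized on these outcomes.

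**Conclusion.** The point holds in limited form. Both diary outcomes are defined as changes, the diary starts with the treatment, and no reference value is fixed. Symptoms have at most one recalled pre-garment day. Treatment use has no scheduled pre-treatment record.

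The size of the harm is unknown. The fall from 80% to between 71% and 29% rests on five assumptions: 45 per arm, a two-sided 0.05 test, a 0.59 SD effect borrowed from the SCORAD sample size, a carry-over of 10% to 50%, and a change-score SD equal to the outcome SD. It shows the direction and possible scale of the loss and is not an estimate for this trial. No single power figure is supported.

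These are secondary outcomes and a valid comparison remains available from planned data, so this is an inexpensive improvement and not a threat to the main result. It is still worth making before enrolment, because a contemporaneous record of eczema medication at Visit 1 cannot be recovered once patients have started wearing the garments.

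**What to change.** - **Itch and sleep:** define the outcome as the between-arm difference in mean on-treatment diary score for each symptom, adjusted for the Visit 1 SCORAD part C itch and sleeplessness scores, which are already collected.
- **Treatment need:** define the outcome as the between-arm difference in days of use of each listed drug class over the eight weeks. Record current eczema medication at Visit 1 and use it as the covariate.
- **Wording:** retitle both outcomes as on-treatment levels, so that no reference period has to be chosen later.

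The cost is a reworded outcome and one extra line on the Visit 1 form. No visit, patient or procedure is added. Issuing the diary earlier to create a run-in is not recommended: the interval between Visit 0 and Visit 1 has no defined length, consent is signed only at Visit 1, and participation would extend beyond the roughly eight weeks stated.

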## 4. Study Design

Double blind, placebo-controlled, parallel randomized study enrolling a sample of patients with medical diagnosis of AD.

The approximate time to complete study enrollment is about 6 months. The expected duration of subject participation is eight weeks, approximately, with one screening visit and two visits after enrollment, one at the beginning and the other at end of the study. During the eight weeks trial the patient will be asked to use cotton Tshirt and cotton pants as pijama during the night.

Visits are performed at an appropriate medical setting at Instituto Cuf, Porto. Each visit lasts approximately 45 min including medical examination, filling of one questionnaire, serum sampling and a superficial skin swab of determined areas.

## 5. Study Enrollment and Withdrawal

### 5.1 Subject Inclusion Criteria

In order to be eligible to participate in this study, a subject must meet all of the following criteria:

- Medical diagnosis of atopic dermatitis
- Age superior to three years old

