## 1. PROTOCOL SUMMARY

| **Title:** | Biofunctional textiles in the management of atopic dermatitis |
| --- | --- |
| **Précis:** | Atopic dermatitis (AD) is a chronic inflammatory skin disease characterized by exacerbations and remission of intensely pruritic lesions of variable location. AD may be acute (short-term and severe) with predominantly redness, vesicles and oozing, or it may be chronic (long-term) with scaling, skin thickening, altered pigmentation and exaggerated surface markings. The condition affects mainly the creases of the elbows and knees, and the face and neck, although it can affect any part of the body. The severity of AD is variable, ranging from localized mild scaling to generalized involvement of the whole body. Itching is the predominant symptom which can induce a vicious cycle of scratching, leading to skin damage. There is a tendency to lifelong dry sensitive skin. Skin of AD is often colonized by Staphylococcus aureus contributing to perpetuating cutaneous inflammation. AD treatment is based on skin hydration, identification and elimination of flare factors, and pharmacologic therapy. Biofunctional textiles are emerging as new and complementary tools . Chitosan is a natural polysaccharide with in vitro anti-microbial activity and regenerating properties. We aim to evaluate the effect of a textile coated with chitosan in management of AD as well as its impact on systemic inflammation and skin flora namely on colonization by Staphylococcus aureus .  Patients with medical diagnosis of AD are selected. Clinical data are collected and written information is provided. After enrollment patients are randomized to active group (cotton textiles impregnated with chitosan) or control group (cotton textiles). Patients are asked to use a Tshirt and pants as pijamas for a period of 8 weeks. Outcomes are clinical improvement measured by SCORAD (severity score of AD including subjective symptoms as sleep disturbance and pruritus and intensity and severity of skin lesions), quality of life, inflammatory serum markers and skin microbiological assays. |
| **Objectives:** | To assess the efficacy of a natural biopolymer textile in the management of atopic dermatitis, and to characterize its immunomodulatory properties and impact on skin microbiological flora . |
| **Setting:** | Immunology Department, Medical Faculty , Porto University |
| **Subjects:** | Portuguese patients, of any gender and any race, aged over 12 years old; |

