### 3.2 Study Outcome Measures

##### 3.2.1 Primary Outcome

- Investigator rated eczema severity

Clinical improvement measured by local SCORAD (score of severity of AD- supplement 1) (initial versus final, % of change).

SCORAD is composed of three different domains (A= extension B= intensity C = subjective symptoms). To determine extent, the sites affected by eczema are shaded on a drawing of a body. The rule of 9 is used to calculate the affected area (A) as a percentage of the whole body: Head and neck 9% Upper limbs 9% each , Lower limbs 18% each , Anterior trunk 18% ,Back 18% 1% each for genitals, each palm and the back of each hand. The score for each area is added up. The total area is 'A', which has a possible maximum of 100%.

A representative area of eczema is selected. In this area, the intensity of each of the following signs is assessed as none (0), mild (1), moderate (2) or severe (3).:Redness ,Swelling ,Oozing / crusting Scratch marks , Skin thickening (lichenification),Dryness (this is assessed in an area where there is no inflammation) .The intensity scores are added together to give 'B' (maximum 18).

Subjective symptoms i.e., itch and sleeplessness, are each scored by the patient or relative using a visual analogue scale where 0 is no itch (or no sleeplessness) and 10 is the worst imaginable itch (or sleeplessness). These scores are added to give 'C' (maximum 20).

- Changes in Quality of life.

Patients are asked to answer the Portuguese version of the Dermatology Life Quality Index (> 16 years old) or the children´s Dermatology Quality of Life Index (4-16 years old) at the beginning and end of the study (supplement 2 and 3)

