### 5.2 Subject Exclusion Criteria

A potential subject who meets any of the following criteria will be excluded from participation in this study if:

- Presence of any significant illness that could interfere with the study, particularly if accompanied by immunological skin abnormalities as psoriasis
- Contact eczema, hand eczema , nummular eczema, other forms of eczema that not atopic eczema
- Anything that, in the opinion of the investigator, preclude the subject’s full compliance with or completion of the study.

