### 10.4. Exclusion of Special Populations

Children under twelve years-old .

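### The protocol states conflicting lower age limits (over three, over 12, not under twelve), so eligibility is contradictory for patients above 3 and up to 12 years.

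*Protocol*

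**What the plan says.** Three places in the protocol set a lower age limit.

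- Section 5.1 opens its list by saying that "a subject must meet all of the following criteria". The list has two entries: a medical diagnosis of atopic dermatitis, and "Age superior to three years old".
- Section 1, in the Subjects row of the summary, has "Portuguese patients, of any gender and any race, aged over 12 years old".
- Section 10.4, headed as the exclusion of special populations, consists of one entry: "Children under twelve years-old".

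Two other sections bear on the point. Section 5.2 introduces its list with "A potential subject who meets any of the following criteria will be excluded from participation in this study if" and gives three criteria, none of them about age. Section 3.2.1 lists quality of life under the primary outcome and assigns two questionnaires by age: a children's index for 4 to 16 years and an adult index for those over 16.

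**The concern.** The three statements cannot all hold for the same child. The discrepancy also sits where it will be acted on. Section 7 has staff decide eligibility at Visit 0 from the inclusion and exclusion criteria, which are 5.1 and 5.2. A five-year-old passes both on age, yet 10.4 bars that child.

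The disputed ages are not a remote corner of the disease. Section 5.3 recruits from paediatric consultations among others, and section 2.1 reports Portuguese eczema prevalence of 9.3% at 6-7 years against 5.2% at 13-14 years. Children under 12 can be expected to present.

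At stake are the population to which the result applies, the standing of any child enrolled under 5.1, and what the ethics committee is asked to approve, since both study visits include serum sampling and skin swabs. There is also a possible knock-on for an outcome listed as primary, if the limit in 5.1 reaches below the youngest age that the children's index covers.

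**Working it through.** No formula applies. The check sets the age statements side by side and reads each one literally.

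| Patient's age | 5.1 inclusion | 5.2 exclusion | Section 1 summary | 10.4 exclusion | Consistent? |
| --- | --- | --- | --- | --- | --- |
| 3 or younger | out | silent | out | out | yes |
| above 3, under 12 | in | silent | out | out | no |
| exactly 12 | in | silent | out | not excluded | no |
| over 12 | in | silent | in | not excluded | yes |

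1. **Range in conflict.** The statements disagree from just above 3 years up to and including 12. They agree on everyone over 12.

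2. **Two conflicts.** The main one is 5.1 against both other sections, for children above 3 and under 12. The smaller one is the summary against 10.4 at age 12: one requires more than 12, the other excludes only those below it.

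3. **How age is counted.** The protocol does not say whether its limits mean time since birth or completed years, and this moves the edges.
   - *Time since birth.* Section 5.1 opens just after the third birthday. Children under 12 in dispute fall in the year-groups 3 to 11, that is 11 − 3 + 1 = 9. Those aged three but not yet four lie below the 4-year start of the children's index and have no quality-of-life instrument. The summary and 10.4 differ only on the twelfth birthday itself.
   - *Completed years.* Section 5.1 opens at 4. The year-groups under 12 in dispute are 4 to 11, that is 11 − 4 + 1 = 8, and no admitted child lacks an instrument. The summary then opens at 13, so all twelve-year-olds are in dispute between it and 10.4.

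   Either way the main conflict remains.

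4. **Does another section settle it?** No. The children's index for 4 to 16 years can be used with either lower limit. The consent procedure for minors in 10.3.1 and recruitment from paediatrics in 5.3 suit adolescents as well as young children. No section gives an order of precedence.

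**The case against.** The best defence is that the sections can be applied together. Section 5.1 gives necessary conditions and 10.4 adds an exclusion, so a strict reader who applies both arrives at 12 and over. That is logically available, but it leaves the three-year criterion with no function, it still disagrees with the summary at age 12, and it requires eligibility staff to find an age rule in the ethics chapter. It softens the contradiction without removing it.

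Several stronger readings are tempting but not supported.

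- **That the whole trial population is undetermined.** It is not; patients over 12 are eligible on age throughout.
- **That 5.1 must be the slip, because two of three sections say 12.** A count of sections does not show intent, and the two do not state the same limit.
- **That three-year-olds will certainly lack a questionnaire.** This holds only if the criterion in 5.1 takes in patients not yet four.
- **That children enrolled under 5.1 would have to be discontinued.** Section 5.4.3 removes a subject found to meet an exclusion criterion, but the list under that name, in 5.2, has no age entry. The consequence requires 10.4 to be treated as part of that list.
- **That power would fall by a calculable amount.** This would need the share of patients under 12, an effect size, a standard deviation, the allocation ratio, the sidedness of the test and a rule that discards such patients. Section 8.2 gives only a significance level of 0.05, power of 0.8 and 90 patients, and no section orders randomised patients to be discarded.
- **That proxy rating would damage SCORAD.** Section 3.2.1 lets the patient or a relative score itch and sleeplessness at any age, so a relative as rater is foreseen whichever limit applies.

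**Conclusion.** The point stands as an internal contradiction in a stated eligibility rule, wrong as written. It covers patients above 3 and up to 12 years. Under 12 that is eight or nine year-groups, depending on how age is counted; a separate and smaller disagreement lies at age 12. The practical consequence follows directly: staff who apply 5.1 and 5.2 as section 7 directs would enrol children whom 10.4 bars.

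This conclusion rests on the wording alone and needs no assumption about recruitment. How many of the 90 patients would be involved is unknown, since the protocol gives no age distribution. The gap in the quality-of-life instruments is conditional on how 5.1 is read. Which limit was intended cannot be decided from the documents.

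**What to change.** Before the first enrolment:

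- The sponsor should decide the intended lower age limit and state it in identical words in sections 1, 5.1 and 10.4. The wording should make clear whether it means a birthday reached or completed years, so that the boundary age is not left open.
- The sponsor should check that limit against the instruments in 3.2.1, so that every eligible patient falls within the children's index (4 to 16 years) or the adult index (over 16).

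The cost is a few lines of text, with ethics review of the changed wording if the protocol has already been submitted. If the higher limit is the intended one, the recruitment pool is smaller than 5.1 now implies. No change to the sample size or the analysis follows from this point.

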### 5.2 Subject Exclusion Criteria

A potential subject who meets any of the following criteria will be excluded from participation in this study if:

- Presence of any significant illness that could interfere with the study, particularly if accompanied by immunological skin abnormalities as psoriasis
- Contact eczema, hand eczema , nummular eczema, other forms of eczema that not atopic eczema
- Anything that, in the opinion of the investigator, preclude the subject’s full compliance with or completion of the study.

